## Background

### Mental health and the burden on health services utilization and health outcomes

Emergency psychiatric care, unplanned hospital admissions and inpatient health care are the costliest forms of mental health care [1]. The frequency of Emergency Department (ED) presentations with mental health concerns and length of psychiatric hospitalizations can have significant physical, psychological, and financial consequences for patients and their families and affect the infrastructural, human, and economic well-being of healthcare systems [2, 3]. This is especially true in the era of the COVID-19 pandemic when already limited services have been further stretched by growing hospital admissions, ED presentations and an increase in extended stays [4–6]. The World Health Organization reported in October 2020 that the pandemic had disrupted or halted critical mental health services in 93% of countries worldwide [7]. Consequently, the increased demand for mental health support has renewed the interest in seeking out solutions to mitigate avoidable hospital readmissions and ED visits, as well as to lower lengths of stay (LOS) in acute care facilities [8].

People with psychiatric disorders have the highest early readmission rates among all hospitalized patients [9–11]. Early readmission is defined as readmission within 30 days of previous discharge [9]. Although deinstitutionalization of care and transition to community-based mental health care has been an approach of focus for decades [12, 13], early hospital readmission rates remain high. In Nova Scotia, the 30-day re-admission rate for inpatient mental health treatment was 10.14% for the 2021/2022 fiscal year. The unmet need for psychological treatment and the limited human resources to address this gap is a major cause of readmission in acute psychiatry units [9]. The readmission rate is a prevalent indicator used for quality assessment of care and a focus of interest for health sector policymakers [14, 15]. In psychiatry, readmission rates are usually commensurate with relapse or complications following an inpatient stay. While it may reflect premature discharge from inpatient psychiatric units, it may also relate to the lack of coordination of post-discharge healthcare services [16, 17].

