**Fig. 3 Fig3:**
[figure not shown]
Study design diagram (**a** Pre-and post-evaluation study; **b** Controlled cohort study)

The cohort study will compare two study populations: the intervention group (IG) consisting of patients attending RASP, and the control group (CG), comprising a cohort of patients who were referred by PHP to the MHAP central intake services prior to RASP implementation (Fig. 3b). This design allows researchers to examine whether possible changes in high-cost health services utilization are associated with the intervention (RASP).

A cross-sectional evaluation of mental health outcomes at program entry will be employed to evaluate the prevalence and correlates of the various psychological conditions of the assisted population.

Patient experience and satisfaction will be assessed using both quantitative and qualitative data. The quantitative data will be extracted from the program's satisfaction survey, while the qualitative data will be gathered from a purposive sub-sample of the overall study population. The selected sub-sample will be invited to participate in focus group discussions as part of a sub-study to gain deeper insights into their experiences and perspectives. Key informant interviews will be conducted to obtain qualitative insights from various healthcare partners, including directors, psychiatrists, primary healthcare providers, MHA service leaders, and community organizations. These interviews will focus on their perceptions regarding the impact of RASP on patients' access to community mental health care and the support it provides for primary care providers. Qualitative descriptive methodology and thematic analysis will be employed to generate and refine the information and identify patterns or themes within the qualitative data [35, 36]. This research protocol has been approved by the Research Ethics Board at Nova Scotia Health (REB file #1028254). The Gantt chart timeline is presented in the supplementary material (Table S1).

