### Participants and data collection

All RASP patients receive a consent form as part of their intake process, allowing access to their health services utilization records. Only those who sign the consent form will be part of the study. While consent is obtained during the initial assessment for ongoing patient recruitment, data collection is scheduled to commence after the program's first year, in April 2024. Service utilization data will extracted from provincial information systems retrospectively and prospectively at 2-time points: one year pre- and one-year post-assessment date at RASP. In addition, sociodemographic and mental health assessment information, including results from patient-completed validated scales and psychiatry diagnosis, and patient satisfaction will be extracted from routine paper-based initial screening forms. Patient satisfaction quantitative data will be extracted from RASP's patient satisfaction survey, available in a paper-based format and completed immediately after the assessment or REDCap online survey link sent via text message to all patients attending the service just after the assessment appointment.

The control group for the cohort study will comprise patients referred to the MHAP Central Intake Services by a PHP before RASP implementation. The periods for inclusion in the control group will be May 2017 to May 2019 (pre-COVID) and May 2020 to May 2022 (during COVID). By examining the data from these two time points (pre-COVID and during COVID) and comparing them with each other and with data during the RASP implementation period, we will be able to evaluate the impact of the pandemic on health services utilization as well as the impact of RASP implementation in comparison with both the pre-pandemic and during the pandemic periods. Ethics approval for exemption from requiring informed consent for all control group patients has been granted by the Research Ethics Board at Nova Scotia Health (REB file #1028254), allowing control group patients' sociodemographic and health services utilization information from provincial administrative databases to be accessed by the investigators.

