For the qualitative component of the study, expected to take place after a year of RASP implementation, in April 2024, a sub-sample from the overall pool of the intervention population (RASP patients) will be invited by a research team member to participate in a focus group session. The inclusion criteria to participate in the qualitative sub-study are to provide consent and be available to attend a 1-hour focus group session, which will be audio-recorded. The focus group script will be developed by investigators, reviewed by healthcare partners, piloted with patients and adjusted as needed, before being used in the focus groups. A trained research team member will conduct the encounters, which may happen in person or via Zoom. The sample size for the qualitative component of the study cannot be predetermined because data saturation needs to be reached. Data analysis ends when no new themes and subthemes emerge across all analysts. However, based on what the literature suggests [37], we anticipate that 25-30 participants may be sufficient for this mixed-methods study. Participants will receive compensation for their time spent participating in the qualitative sub-study activities.

Healthcare partners involved with RASP will be also actively engaged in the qualitative evaluation of the program. Trained members of the research team will conduct individual key informant interviews, either virtually or in person, with program directors, psychiatrists, primary healthcare providers, MHA service leaders, and representatives from community organizations. These interviews aim to gather in-depth information about healthcare partners' experiences and opinions regarding the program, allowing for a comprehensive understanding of their perspectives.

Finally, a sub-population of RASP patients who opted to participate in the Text4Support RCT will also have their one-year pre- and post-RASP attendance health services utilization data collected and compared to patients who chose not to participate in the optional Text4Support RCT. RASP was launched in April 2023, with data collection ongoing. Table S2 demonstrates in detail the variables, sources and data collection time points.

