### Data analysis

#### Quantitative analysis

Quantitative data will be analyzed using descriptive and inferential statistics by using SPSS version 26 for Windows [46]. First, we will summarize the study participants' sociodemographic and clinical descriptive characteristics. Primary outcomes comparing the pre-and post-enrollment health services utilization for patients accessing RASP will be analyzed using descriptive and inferential statistical analysis, including Chi-Square and independent sample t-tests. For the primary outcome involving control populations, pre- and post-enrollment health services utilization variables will initially be compared using an analysis of covariance (ANCOVA) with the intervention condition (attended RASP) as the independent variable, the relevant health services utilization data one year pre attendance of appointment with RASP psychiatrist or community mental clinician as the covariate, and the relevant high-cost health services utilization data one year post attendance of appointment with a RASP psychiatrist or attendance with mental health clinicians in the community mental health program as the dependent variable. In each case, checks would be conducted to ensure no violation of regression slopes and reliable measurement of the covariate. We will perform sensitivity analyses of covariance to explore the impact of the imputation of data loss at each time point on health services utilization. In addition, we will perform propensity score matching and regression analyses adjusting for the periods pre-, during and post COVID-19 pandemic in order to strengthen the comparability of the groups and enhance the validity of the study's findings.

We will also use an ANCOVA to compare high-cost health services utilization data for one-year pre- and post-RASP attendance for the subset of patients who attend RASP and either participate or do not participate in the Text4Support RCT. For this analysis, the intervention condition (participants in the Text4Support RCT) will be the independent variable, the relevant health services utilization data one-year pre-attendance of appointment with RASP psychiatrist will be the covariate, and the relevant high-cost health services utilization data one-year post attendance of appointment with a RASP psychiatrist will be the dependent variable.

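### The RASP effect cannot be adjusted for a post-COVID period that contains every RASP patient and no control

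*Protocol article*

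**What the plan says.** Four statements in the protocol article bear on this.

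- **Controls.** Study design defines the control group as "patients who were referred by PHP to the MHAP central intake services prior to RASP implementation". Participants and data collection fixes the dates: "The periods for inclusion in the control group will be May 2017 to May 2019 (pre-COVID) and May 2020 to May 2022 (during COVID"). No third control window is given.
- **RASP patients.** The same section states that "RASP was launched in April 2023, with data collection ongoing".
- **Model.** Quantitative analysis specifies an ANCOVA "with the intervention condition (attended RASP) as the independent variable", with the same type of service use in the year before attendance as covariate and use in the year after as outcome. It then adds that "we will perform propensity score matching and regression analyses adjusting for the periods pre-, during and post COVID-19 pandemic", and gives the purpose: "in order to strengthen the comparability of the groups and enhance the validity of the study's findings".
- **Claim.** Participants and data collection says of these comparisons that "we will be able to evaluate the impact of the pandemic on health services utilization as well as the impact of RASP implementation", relative to both the pre-pandemic and the pandemic control periods.

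Outcome measures makes the between-group comparison part of the primary outcome. Hypothesis expects a reduction of at least 10% in it.

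**The concern.** A period adjustment can separate the programme from calendar time only if at least one period contains both RASP patients and controls. On the stated dates none does. Pre-COVID and COVID-era patients are all controls, and everyone from April 2023 onward is a RASP patient. The step offered as protection against calendar differences therefore cannot remove the one that matters most, which is change between the control windows and the RASP era.

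The Background describes the pandemic era as one of "growing hospital admissions, ED presentations and an increase in extended stays". If use was raised in one control window, or has moved again since 2022, part of the RASP contrast is calendar change. A reader told that the estimate was adjusted for period would think this had been dealt with. The same comparison feeds the net cost savings in Health economic evaluation.

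**Working it through.** The plan gives no figure to reproduce. The question is whether the effect can be identified, so the check is on the model.

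**1. Assign periods from the stated dates.**

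| Period | Controls | RASP patients |
|---|---|---|
| Pre (May 2017 to May 2019) | yes | none |
| During (May 2020 to May 2022) | yes | none |
| Post (April 2023 onward) | none | all |

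**2. Write the model.** Let R = attended RASP, X = prior-year use, D = during, P = post, with pre as reference:

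E[Y] = a + bR + cX + dD + eP.

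R = P for every patient, so E[Y] = a + (b + e)R + cX + dD. Only the sum b + e can be estimated. The RASP effect b cannot.

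**3. Rank.** With 2,500 patients per window (illustrative; Sample size considerations expects at least 2,500 per group), the columns intercept, R, X, D, P number 5 and have rank 4. With only the May 2020 to May 2022 controls, the window named in Sample size considerations, the columns intercept, R, X, P number 4 and have rank 3. A larger sample does not change this.

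**4. Simulation.** Control mean 10, SD 1 and during-COVID shift +0.5, all assumed for the simulation:

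| True RASP effect | True post-period shift | Coefficient, reference pre | Coefficient, reference during |
|---|---|---|---|
| 0 | −1 | −1.00 | −1.50 |
| −1 | 0 | −1.00 | −1.49 |
| −0.5 | −0.5 | −0.98 | −1.48 |

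The three truths give the same answer within simulation error, and the answer moves with the reference window.

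**5. What remains when a redundant column is dropped.** If R is dropped, there is no RASP estimate. If P is dropped, the RASP coefficient is RASP minus the reference window. Take no RASP effect, assumed period means, equal-sized control windows and no baseline adjustment:

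| Means (pre / during / post) | Against pre | Against during | Against pooled controls |
|---|---|---|---|
| 1.0 / 1.2 / 1.0 | 1.0/1.0 − 1 = 0% | 1.0/1.2 − 1 = −16.7% | 1.0/1.1 − 1 = −9.1% |
| 1.0 / 1.15 / 0.9 | 0.9/1.0 − 1 = −10% | 0.9/1.15 − 1 = −21.7% | 0.9/1.075 − 1 = −16.3% |

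**6. Propensity score.** If period enters that model, P(RASP | period) is 0, 0 and 1, which is complete separation, and no pair can be matched within a period.

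**7. Could a few late controls rescue the model?** The outcome year runs from attendance, so a control referred near May 2022 who waited long might be seen in 2023. If k of the controls counted as post, the standard error of the RASP effect would be 0.317 SD for k = 10, 0.143 SD for k = 50 and 0.066 SD for k = 250. The nominal value with 2,500 per group is √(2/2500) = 0.028 SD. The effect would be estimable but would rest almost entirely on those few patients. The article plans no such coding.

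**The case against.** Several points on the other side stand.

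- **The period term is not inert.** A reader might infer that the adjustment does nothing. In the first scenario of step 5, leaving period out and pooling the controls gives a false 9.1% reduction, while including it with pre-COVID as reference gives 0%, the correct answer. A COVID surge that fully reverts is avoided in the pre-COVID contrast. It also follows that not every scenario produces a spurious reduction near 10%.
- **Baseline adjustment helps.** The ratios in step 5 ignore the planned prior-year covariate. If a period shift raises both years equally, the ANCOVA leaves shift × (1 − slope): at an assumed slope of 0.5, 0.20 × 0.5 = 0.10, or half. It helps less for a control seen in mid-2020, whose prior year is mostly pre-pandemic and whose outcome year is not.
- **Matching need not fail.** A reader might infer that no propensity matching is possible. The sentence can be read as matching, plus separate regressions adjusted for period. Matching on sociodemographic factors and prior use would remain feasible.
- **Estimable contrasts are already announced.** Participants and data collection describes comparing RASP with each control period.
- **The label is inferred.** The article never calls the RASP era post-COVID. But the other two levels are assigned to controls, and no other patients could fill the third.
- **The step is additional.** It follows the ANCOVA, and the within-subject primary comparison does not use it, although that comparison has no concurrent control either.

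None of this makes the three-level adjustment estimable. Collapsing to pandemic versus non-pandemic would do so only by assuming that 2017 to 2019 and 2023 onward are interchangeable, which the article does not state. Nor is this a detail left to a fuller plan: the article names the method, its purpose and the dates, and these conflict.

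**Conclusion.** The point holds, and the text needs correcting. On the stated dates, the RASP effect adjusted for a three-level period factor does not exist as an estimable quantity. What software returns is either no RASP estimate or a contrast with whichever window is the reference. Change specific to 2023 onward cannot be separated from RASP, so the claim to evaluate RASP's impact apart from calendar period is unsupported.

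The non-identifiability rests only on the inclusion windows, the April 2023 launch and period being coded by inclusion window. The size of any bias is unknown. Under the two assumed sets of period means, before baseline adjustment and with no RASP effect, the apparent reduction runs from 0% to 10% against pre-COVID controls and from 16.7% to 21.7% against COVID-era controls, next to a hypothesised 10%. The documents do not support the stronger readings that the adjustment has no effect on the result or that nothing can be matched.

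**What to change.** 1. Remove the three-level period term from the regression, and state that period does not enter the propensity model.
2. Pre-specify two baseline-adjusted contrasts, RASP versus pre-COVID controls and RASP versus COVID-era controls. Report them separately and require the between-group conclusion to hold against both.
3. State beside each result that it contains RASP plus calendar change.
4. Reword Quantitative analysis and Participants and data collection so that neither promises to separate RASP from period.

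This changes wording and pre-specification only and needs no new data. The price is a more modest between-group claim.

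Two additions are optional. A sensitivity analysis could use primary-care referrals from June 2022 to March 2023. With follow-up stopped at the RASP launch, these give at most about ten months from referral and less from attendance, so they do not meet the one-year endpoint and would favour patients seen quickly. They also need a further extract and a wider date range in the control-group consent exemption. A negative-control outcome, such as emergency visits not related to mental health, could be added if the data are available. The article plans only mental-health-specific visits, and other visits need not follow the same trend.

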#### Health economic evaluation

We will conduct an economic evaluation through an effectiveness-implementation science lens. Specifically, we will conduct a cost-consequence analysis (CCA) from a Canadian single-payer perspective. The CCA will involve a disaggregated comparison of the costs and benefits (consequences) associated with RASP. The disaggregated analysis reports the intervention effects for the relevant primary and secondary outcomes in their natural units to aid value for money assessments. The study design, population, setting, and location are described elsewhere in this proposal.

We will compare outcomes (ED visits, crisis calls and inpatient days) and costs in the intervention group to the control group. Costing includes costs associated with the pre-implementation, implementation, and ongoing costs. These costs will include space and utilities, new hires specific to RASP, supplies, materials, and equipment, travel costs, volunteer time, and other in-kind donations. We will exclude all research-related costs. These cost data will come from the project documents. In addition, we will collect cost data on health resource use from the case costing centre in the Nova Scotia Health, supplemented with data from the literature if necessary.

Costing will also include costs saved from avoided ED visits, crisis response services and inpatient treatments. Cost analyses will use Nova Scotia Health 2023 costs to ensure relevance to decision-makers. We will estimate the intervention effect for the outcomes using appropriate treatment-effect econometric models with bootstrapping to quantify the uncertainty around the estimates. To enable cost comparisons, the cost of the current models of community-based mental health services, which involve waitlisting of all non-urgent patients (regardless of referral source and reason for referral) to see a mental health clinician as a gateway to receipt of community mental health services, including psychiatry, will be compared with the costs of alternative treatments offered expeditiously through RASP and primary care and community providers. We will compute the net cost savings associated with RASP. Our economic analysis will follow guidelines for economic evaluations, including using probabilistic sensitivity analysis to quantify the uncertainty around the implementation costs [48].

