The study seeks to address the following research questions:A.Effectiveness and Impact on Health Services Utilization of the RASP:Did RASP increase the volume of patients referred by PHP? Measured by the number of patients referred by a PHP for a psychiatrist consultation before and after RASP implementation.Did RASP increase the proportion of patients triaged by Central Intake services who had direct access to psychiatric consultations? Measured by the proportion of referrals received by central intake that were booked directly for psychiatry consultation, before and after RASP implementation.Did RASP reduce wait times for access to psychiatrists in the publicly funded MHAP? Measured by the number in calendar days waiting from date referral was received by Central Intake to date patient is scheduled for a psychiatric consultation before and after RASP implementation.Did RASP improve efficiency of the Community Mental Health Programs (CMHP) to address the mental health needs of patients with complex mental health needs? Measured by wait-times for assess to psychiatrists within the CMHP following a referral by a mental health clinician before and after RASP implementation.Did RASP reduce the volume of patients referred by PHP to the ED for a psychiatric consultation? Measured by the number of patients referred by a PHP for a psychiatrist consultation at the ED before and after RASP implementation.Did RASP reduce ED visits, mobile crisis visits, and inpatient mental health services utilization? Measured by the number of mental health and addictions (MHA)-specific ED visits, number of mobile crisis visits, number of MHA-specific hospital admissions, and number in calendar days in LOS for Central Zone patients, before and after RASP implementation.Did patients who attended the RASP and opted to participate in the Text4Support RCT differ in their health services utilization compared to patients who opted not to participate in the Text4Support RCT? Measured by the number of MHA-specific ED visits, number of mobile crises calls, number of MHA-specific hospital admissions, and LOS in calendar days, one-year post-RASP assessment.What are the costs and benefits to Nova Scotia Health from having a RASP for mental health? Measured by the net cost savings associated with RASP considering costs associated with the program and costs saved from avoided high-cost health services utilization (ED visits, mobile crisis visits, and inpatient treatments).B.Perspectives and Experiences of Healthcare Partners and PatientsWhat are healthcare partners' perceptions related to the impact of the RASP on access to community mental health care for patients and support for primary care providers? Measured by qualitative data from key informant interviews with program directors, psychiatrists, primary healthcare providers, MHA service leaders, and representatives from community organizations.What are the patients' perceptions related to their overall experience and satisfaction with the service received? Measured by quantitative and qualitative data from the RASP's satisfaction survey and qualitative data from focus group sessions with a sub-group of the assisted population.C.Population Characteristics and Mental Health MeasuresWhat proportion of patients seen at the RASP continued their treatment with PHP? Measured by the number of patients fully discharged back into the care of their primary healthcare provider with treatment recommendations (chart review data).What proportion of patients seen at the RASP were referred to a community mental health program? Measured by the number of patients referred to a community mental health program by RASP psychiatrists (chart review data).What proportion of patients seen at RASP needed additional psychiatric evaluation at the RASP? Measured by the number of re-referrals to RASP by a PHP.What are the sociodemographic characteristics of the assisted population at program entry? Measured by the frequency and percentages of the sociodemographic characteristics (e.g. age, sex of birth, gender, ethnicity, employment status, source of income, income range, relationship status, family support, housing status, education, provincial zone) (chart review data).What is the status of patients’ recovery and health quality index, and the prevalence of likely major depressive disorder (MDD), likely generalized anxiety disorder (GAD), low resilience, childhood trauma, substance use, and suicide risk at program entry? Measured by patient-completed validated scales scores (chart review data).What is the prevalence of patients' diagnoses made by RASP psychiatrists at program entry? Measured by the frequency and percentages of each psychiatry diagnosis after psychiatry assessment (chart review data).What are the risk factors for ED presentation for mental health concerns and inpatient psychiatric treatments? Measured by Odds Ratios using logistic regression models with sociodemographic and clinical data from the assisted population one year before and after RASP assessment date.

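### The cost analysis takes a single-payer perspective but counts volunteer time and donated resources as program costs, so the payer's net saving would be understated by whatever those items are worth.

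*Protocol article*

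**What the plan says.** The Health economic evaluation section sets the viewpoint: "we will conduct a cost-consequence analysis (CCA) from a Canadian single-payer perspective". The cost question under Study objectives names the same payer: "What are the costs and benefits to Nova Scotia Health from having a RASP for mental health". Its measure is given in the same place: "Measured by the net cost savings associated with RASP considering costs associated with the program and costs saved from avoided high-cost health services utilization".

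The Health economic evaluation section then defines what is charged to the program. "Costing includes costs associated with the pre-implementation, implementation, and ongoing costs". The items listed run from premises, dedicated staff and equipment to "travel costs, volunteer time, and other in-kind donations". One exclusion is stated: "We will exclude all research-related costs". The section also commits to a single summary figure: "We will compute the net cost savings associated with RASP".

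No section says that items not paid for by the payer will be left out of the payer total, shown apart from it, or analysed under a second, broader perspective.

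**The concern.** The perspective of an economic evaluation determines which costs count. Under a payer perspective, a cost counts if the payer bears it. Volunteers' hours and goods given by outside parties are real resources, but someone else provides them, so they belong to a broader (for example societal) perspective. The plan declares the first perspective and lists items from the second.

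What is at stake is the net saving. It is a difference between two sums, avoided service cost and program cost, so an item wrongly placed in one of them passes into the difference in full. The section chooses its price basis so that the results are relevant to decision-makers. A payer who reads one net figure will take it to contain the payer's own costs.

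**Working it through.** The article reports no cost amounts, so there is no figure to reproduce. The check is an accounting identity, followed by an illustration on assumed ratios.

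**Inputs from the article**
- Perspective: single payer (Health economic evaluation).
- Target quantity: net cost savings to Nova Scotia Health (Study objectives, cost question).
- Program cost: includes volunteer time and other in-kind donations; only research costs are excluded (Health economic evaluation).

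**Notation**
- S = cost of avoided ED visits, mobile crisis visits and inpatient treatment.
- C = program cost borne by the payer.
- V = value placed on volunteer time and on donated resources not supplied by the payer.

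**Identity**
- Net saving to the payer = S − C.
- Net saving as the plan defines it = S − (C + V).
- Difference = −V.

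For any V above zero the payer's saving is understated by exactly V. The error works against RASP.

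**Relative size, on assumptions**

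Let g = S/C and s = V/C. The understatement as a share of the payer's net saving is V/(S − C) = s/(g − 1). Neither s nor g is in the article. The values below only show how the result behaves.

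| g (gross saving / program cost) | s = 2% | s = 5% | s = 10% |
|---|---|---|---|
| 1.1 | 20% | 50% | 100% |
| 1.2 | 10% | 25% | 50% |
| 1.5 | 4% | 10% | 20% |
| 3.0 | 1% | 2.5% | 5% |

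Examples: 0.05/0.2 = 25%; 0.10/0.5 = 20%; 0.10/2 = 5%; 0.10/0.1 = 100%.

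The relative error grows without limit as g approaches 1, so the large entries describe a program close to break-even. If gross savings are several times program cost, or if V is close to zero, the error is negligible.

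**The case against.** **The items may be worth little, or may partly be payer costs.** The Sample size considerations section describes staffing as two psychiatrists and a clinical coordinator, and the program description mentions no volunteers, so the list may be a generic costing checklist. In-kind resources could also come from within the health authority, in which case they are legitimate payer costs. Travel is listed without saying who pays, and nothing suggests that patients do. All of this stands as a limit on size. It does not resolve the conflict, because volunteer time cannot be read as a payer cost and the plan says that it will be included.

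**The analysis is disaggregated, so a reader could take the items out.** This is partly right: line-item cost reporting is plausible. But the sentence that explains the disaggregation concerns intervention effects in natural units, and no payer-only cost total is promised. The probabilistic sensitivity analysis on implementation costs would vary the size of the items without changing where they are counted.

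**The error is conservative.** This is true. It cannot produce a false saving in favour of RASP. An understated saving still gives the payer a wrong answer to the question asked.

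**Stronger readings that the article does not support.** A reader might infer that the hypothesis of 10% cost savings is at risk. The Hypothesis section ties that saving to the reduction in utilization, and Outcome measures defines the cost outcome as costs related to high-cost services. On that natural reading no program cost enters it. A reader might also infer that the comparator carries no matching volunteer or donated items. The article gives no itemised list for the comparator, and silence in a condensed article does not show that they are absent.

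**Conclusion.** The costing rule is wrong as written. It places at least one item that the payer does not bear, volunteer time, in the program cost used for a net saving stated from the payer's perspective. Other in-kind donations fall under the same criticism unless the health authority supplies them.

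The consequence is conditional. If these items are valued above zero and kept in the total, the payer's net saving is understated by exactly their value. The amount cannot be stated from the article. It matters only if the net saving is thin relative to program cost, and it is negligible if the items are small or gross savings far exceed program cost. It would go too far to say that the reported saving will certainly be materially wrong.

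The point is confined to the net cost saving. The utilization outcomes and the sample size are unaffected, and so is the 10% hypothesis on its natural reading. It is a minor point, worth correcting because the correction costs almost nothing.

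**What to change.** State in the Health economic evaluation section that the base-case net saving contains only costs borne by the payer, and say who bears the travel costs. Report volunteer time and externally donated resources on a separate line outside the payer total. Resources supplied by the health authority itself stay in the payer total.

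Alternatively, if a broader view is wanted, declare it as an additional perspective with its own net figure, and apply the same cost items to the comparator.

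The first option costs one sentence and one table row. The items are already to be collected, so it needs no new data. The alternative would also require the same items to be costed for the comparator.
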